### Concealment mechanism {16b}

After obtaining the signed informed consent, the participants will be randomly assigned to the standard or additional capnographic monitoring group according to the central randomization system. The random results, random number, and their relationship with groups will be kept confidential from the participants throughout the trial. The same nasal cannula with a CO_2_-collecting device will be used in both groups and connected to the capnographic monitoring device. The participants will not be aware of their own and others’ grouping before, during, and following gastrointestinal endoscopy.

### Implementation {16c}

Designated doctors will generate the allocation sequence, enroll participants, and assign participants to interventions.

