## Assignment of interventions: allocation

### Sequence generation {16a}

In this trial, we used stratified blocked randomization to design the central randomization system. Risk factors for hypoxia during sedated gastrointestinal endoscopy include patient factors, sedation factors, and endoscopic operation factors. Patient factors mainly include preexisting cardiopulmonary disease, obesity, and advanced age. The incidence of hypoxia during sedated gastrointestinal endoscopy varies among patients with different underlying conditions. However, the subjects in our trial were all ASA I–II patients and did not include patients with ASA III-IV, which means that the trial did not involve patients with previous severe cardiopulmonary disease. Additionally, the number of obese patients in the older population in China is extremely low, and stratification by obesity would provide little benefit. Our study only included ASA I–II older patients aged 65 to 80 years, who we can assume have similar physical conditions, and the incidence of hypoxia during sedated gastrointestinal endoscopy is approximately the same. Therefore, we did not stratify them by age, and only central stratification was used in our trial. Complete baseline data will be collected from participants, including name, gender, date of birth, etc. After assessing patient eligibility for inclusion, his/her informed consent will be obtained. We will randomly assign the participants in a ratio of 1:1 to the standard or additional capnographic monitoring group according to the allocation sequence of the central randomization system. The length of a random sequence is not fixed, and 4, 6, and 8 are random.

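### Item 16c gives sequence generation, enrolment and assignment to one role, contradicting the central randomization system and leaving upcoming allocations unprotected from recruiting staff

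*Protocol article*

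**What the plan says.** All references are to the protocol article.

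- **Implementation {16c}**, a single sentence: "Designated doctors will generate the allocation sequence, enroll participants, and assign participants to interventions".
- **Sequence generation {16a}** describes a different arrangement: "we used stratified blocked randomization to design the central randomization system". Patients are assigned "according to the allocation sequence of the central randomization system". Stratification is by centre only ("only central stratification was used in our trial"), and block sizes vary: "The length of a random sequence is not fixed, and 4, 6, and 8 are random".
- **Concealment mechanism {16b}** places allocation after consent: "After obtaining the signed informed consent, the participants will be randomly assigned to the standard or additional capnographic monitoring group". It then states from whom the allocation is hidden: "The random results, random number, and their relationship with groups will be kept confidential from the participants throughout the trial". The rest of that section concerns the identical cannula and patients' unawareness of their group.
- **Who will be blinded {17a}** confirms that participants alone are blinded.
- **Participant timeline {13}** has the investigator screen patients and seek consent in the endoscopy room, immediately before allocation.

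**The concern.** SPIRIT item 16c exists to show that whoever prepares the sequence is separate from whoever recruits. Here the answer names one role for all three tasks. Someone who knows the next assignment can decide whether to approach a particular patient now, later or not at all. That decision comes before consent, so putting allocation after consent does not guard against it. Varying the block size does not help either, because it only hinders guessing from past assignments.

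Several features raise the stakes in this trial. Staff deliver care knowing the arm. Eligibility is settled on the spot. Section {16a} itself lists obesity, advanced age and cardiopulmonary disease as risk factors for hypoxia, some of which a recruiter can see, yet only centre is a stratification factor. The hypoxia comparison in the Statistical analysis plan section is an unadjusted chi-square or Fisher's exact test.

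**Working it through.** **1. The sections side by side**

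| Question | {16a} and {16b} | {16c} |
|---|---|---|
| Where does the sequence come from? | The central randomization system | Designated doctors |
| Who assigns? | The central system, after consent | Designated doctors |
| From whom is it hidden? | Participants | Not stated |

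There are two readings. If the central system generates and holds the list and releases one assignment at a time, {16c} is wrong as written. If doctors generated the list, {16c} is right and those who recruit may know upcoming assignments. On either reading, no sentence hides the sequence from recruiting staff.

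**2. The plan's own figure**

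The point does not depend on the sample size, but it supplies the number per arm. For 8% versus 4%, two-sided 5% and power 0.90, the continuity-corrected formula gives 788 per arm. Then 788 / 0.90 = 875.6, rounded up to 876, or 1,752 in total, within 3% of the stated ~1800. Evaluable patients per arm: 1800 × 0.90 / 2 = 810.

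**3. What knowing the list adds**

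A simulation used 600 patients per centre (an assumed equal split of 1800 over three centres) and random blocks of 4, 6 and 8. Staff who know only past assignments and guess the under-represented arm are right about 68% of the time. Someone holding the list is right 100% of the time.

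**4. Illustrative size of the bias**

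From the documents: overall risk 8%, and 810 per arm. Assumed, because the documents give no such figures: no true effect, a share *h* = 10% of patients recognisably at high risk, and threefold risk in that group.

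- Base risk *r*: 0.9*r* + 0.1 × 3*r* = 0.08, so *r* = 0.0667 and high risk = 0.20.
- If a fraction *s* of high-risk patients goes to control, the high-risk share is 2*hs* in control and 2*h*(1 − *s*) in the capnography arm.
- SE = √(2 × 0.08 × 0.92 / 810) = 0.0135.
- Probability of rejection ≈ Φ(*z* − 1.96) + Φ(−*z* − 1.96), where *z* = difference / SE.

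| *s* | Control rate | Capnography rate | *z* | Type I error |
|---|---|---|---|---|
| 50% | 8.00% | 8.00% | 0 | 5% |
| 60% | 0.12 × 0.20 + 0.88 × 0.0667 = 8.27% | 0.08 × 0.20 + 0.92 × 0.0667 = 7.73% | 0.40 | 0.059 + 0.009 ≈ 7% |
| 75% | 0.15 × 0.20 + 0.85 × 0.0667 = 8.67% | 0.05 × 0.20 + 0.95 × 0.0667 = 7.33% | 0.99 | ≈ 17% |
| 100% | 0.20 × 0.20 + 0.80 × 0.0667 = 9.33% | 6.67% | 1.98 | ≈ 50% |

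**5. Range over the assumed inputs**

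- Twofold risk, *h* = 10%: *r* = 0.08 / 1.1 = 0.0727. At *s* = 60% the difference is 0.04 × 0.0727 = 0.0029, *z* = 0.22, type I error about 5.5%. At *s* = 100% the difference is 0.2 × 0.0727 = 0.0145, *z* = 1.08, about 19%.
- Threefold risk, *h* = 20%: *r* = 0.08 / 1.4 = 0.0571. At *s* = 60% the difference is 0.08 × 0.1143 = 0.0091, *z* = 0.68, about 10%.

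At 60/40 steering the type I error therefore runs from about 5.5% to 10% over these inputs.

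**The case against.** The strongest reply is that allocation runs through a central system. Sections {26a}, {6b}, {13}, {16a} and {16b} all say so, and several place it after consent. If that system alone holds the list, concealment is intact and {16c} is a poorly condensed sentence. This stands in part: a reader might infer from {16c} that concealment was defeated, and the documents do not establish that. They show a contradiction and a missing safeguard.

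A reader might also infer that the same individual generates the list and recruits at the bedside. The text names a role, not a person, and different doctors may do each task. It does not say so, though, and nothing in {16b} bars one from seeing what another produced.

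A third tempting inference is that steering could be neither detected nor corrected. That is too strong. Table 3 schedules medical history, demographics, vital signs and physical examination at baseline; baseline data are to be compared; and {20b} includes multivariable-adjusted logistic regression. Gross steering on recorded traits would probably show. What remains is steering on clinical impressions that nobody records. The regression is also only an additional analysis, and its outcome is total hypoxia rather than the primary outcome.

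Finally, the magnitudes rest on assumed inputs. Section {16a} takes hypoxia risk to be similar across these ASA I–II patients, and Table 1 excludes patients with chronic obstructive pulmonary disease or a need for supplemental oxygen. This objection stands: the figures show the mechanism and are not a forecast. The procedural point does not depend on them.

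It does not help to say that an SAP or the full protocol may give more detail. The defect is what {16c} affirmatively states.

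**Conclusion.** The concern holds as a contradiction between {16c} and {16a}–{16b}, together with a concealment statement that covers participants only in a trial whose staff are unblinded. As written, upcoming allocations are unprotected from recruiting staff. Whether any recruiter saw the sequence cannot be told from the article.

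Under the assumptions of 10% high-risk patients, threefold risk, 810 per arm and no true effect, 60/40 steering gives a type I error of about 7%. The figure of about 50% requires every high-risk patient to be steered to control; it is an extreme bound and should not carry the argument. The point must be resolved because concealment from recruiters underpins the randomized comparison, and clarifying it is cheap.

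**What to change.** 1. **Establish the facts first.** Determine who generated the sequence, who holds it and who has had access. Under Trial status the study started on September 1, 2021, so this may concern patients already enrolled.
2. **Rewrite {16c}.** The central system, or a statistician with no part in recruitment or care, generates and holds the sequence. Recruiting doctors have no access to the list or to the block sizes. Each assignment is released singly, and only after an eligible, consented patient has been irrevocably registered.
3. **Extend {16b}** so that the sequence is concealed from investigators as well as participants, and keep this distinct from the blinding of patients.
4. **If recruiting doctors did have access**, regenerate the unused part of the sequence, since changing access rights does not remove what they already know, and report who had access.

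If the central system always held the list, the cost is a correction of wording. If it did not, the cost is a change of access rights in a system already in use, a regenerated list for the remaining patients, and disclosure in the trial report. Neither case changes the sample size.

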## Assignment of interventions: blinding

### Who will be blinded {17a}

After the interventions are assigned, only the trial participants will be blinded. The results in the central randomized system will be kept confidential from the participants throughout the entire trial. The same nasal cannula will be used in both the standard and additional capnographic monitoring group, and the sampling line will be connected to a portable beside monitor. The researcher will ensure that participants are not aware of their own or other’s assignment.

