**Step 2: Please DESCRIBE the adverse event(s). Check all that apply.**				
**Minimal risk descriptors**	**Minor risk descriptors**		**Sentinel risk descriptors**	
□ Vomiting/retching	□ Oxygen desaturation (75–90%) for < 60s		□ Oxygen desaturation, severe (<75% at any time) or prolonged (<90% for >60s)	Other, specify below
□ Sub-clinical respiratory depression^a^	□ Apnoea not prolonged		□ Apnoea, prolonged (>60s)	
□ Muscle rigidity, Myoclonus	□ Airway obstruction		□ Cardiovascular collapse/shock^g^	
□ Hypersalivation	□ Failed sedation^e^		□ Cardiac arrest/absent pulse	
□ Paradoxical response^b^	□ Allergic reaction without anaphylaxis			
□ Recovery agitation^c^	□ Bradycardiat^f^			
□ Prolonged recovery^d^	□ Tachycardia^f^			
	□ Hypotension^f^			
	□ Hypertension^f^			
	□ Seizure			

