### Outcomes {12}

#### Primary outcome measures

The primary outcome of this study is the incidence of hypoxia (75% ≤ SpO_2_ < 90% for <60 s) in the two groups from the beginning to the end of the operation.

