#### Secondary outcome measures

The secondary outcomes comprise the following:The incidence of subclinical respiratory depression (90% ≤ SpO_2_ < 95%) in the two groups from the beginning to the end of the operation.The incidence of severe hypoxia (SpO_2_ < 75% or 75% ≤ SpO_2_ < 90% for ≥60 s) in the two groups from the beginning to the end of the operation.The incidence of other AEs recorded via tools proposed by the World Society of Intravenous Anesthesia International Sedation Task Force.

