**Others**						
Gastroscope procedure time				**×**		
Combined medication	**×**	**×**	**×**	**×**	**×**	**×**

When the participants will enter the gastrointestinal endoscopic operating room, they will be screened for eligibility by the investigator. If they meet the inclusion criteria but not the exclusion criteria, the investigator will provide them with the fully informed consent form. After signing the informed consent form, the patients will be allocated to either the capnographic monitoring group or the control group via the central randomization system.

In the capnographic monitoring group, the criteria for apnea is the absence of exhaled CO_2_; altered ventilation is defined as end-tidal CO_2_ reduced by more than half of the baseline, as shown by the capnogram; and the definition of hypoxia is 75%<SpO_2_ < 90%, <60s. In the control group, hypoxia is defined as SpO_2_ <90%.

In both the groups, any sign of apnea, altered ventilation, or hypoxia that prompts an intervention will comprise (i) increasing oxygen supplementation, (ii) a chin lift or jaw thrust maneuver, (iii) insertion of the oropharyngeal or nasopharyngeal airway with a chin lift or jaw thrust maneuver, (iv) artificial mask ventilation, and (v) tracheal intubation.

The duration of surgery is defined as the time from the beginning to the end of the gastrointestinal endoscopy, excluding the time of resuscitation.

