Therefore, future research should seek to resolve some of the limitations of this study. First, this was a single-blinded clinical study, which might cause potential bias. Second, our trial is not international, and the participating institutions of our experiment are all Grade III Class A general hospitals in China. The medications or methods of sedation vary among different institutions and countries. Fortunately, the selected intravenous anesthetics are widely used owing to their clinical compatibility, and the data obtained in our study could be represented in most clinical settings. Third, only older patients with ASA grades I–II were included in our trial, and those with ASA grades III–IV were excluded. We planned another group to be explored in the next study for older patients with higher ASA classifications. Therefore, further capnography monitoring research in gastrointestinal endoscopy under sedation is warranted.

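### Only participants are blinded, so whoever sorts a brief desaturation into the primary outcome knows the arm, and the article describes no masked classification

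*Protocol article*

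**What the plan says.** On masking, the section Who will be blinded {17a} is explicit: "After the interventions are assigned, only the trial participants will be blinded".

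On the endpoint, Primary outcome measures reads "The primary outcome of this study is the incidence of hypoxia (75% ≤ SpO_2_ < 90% for <60 s", counted from the start to the end of the operation. The neighbouring category, under Secondary outcome measures, is "The incidence of severe hypoxia (SpO_2_ < 75% or 75% ≤ SpO_2_ < 90% for ≥60 s". One dip therefore falls on one side or the other according to its depth and its duration against 60 s.

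On capture, Plans for assessment {18a} has trained physicians collecting the data, and Data management {19} has them entered on a case report form. Neither section mentions a masked assessor, a stored oximetry trace or a rule-based derivation. Table 2, Step 2 has an event box worded "Oxygen desaturation (75–90%) for < 60s", which mirrors the primary definition.

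The Discussion lists as a limitation that "this was a single-blinded clinical study, which might cause potential bias" and attaches no safeguard to it.

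**The concern.** Blinding the participants does little for this endpoint. They are sedated and do not report their own saturation. What decides the outcome is whether staff notice a short dip, accept it as real rather than artefact, and place it below or above 60 s. Those staff know the allocation. Under Intervention description {11a} they also watch different displays: a CO2 waveform and values in one arm, the oximetry readout alone in the other.

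The SpO2 number is objective; counting and timing a brief episode is less so. If either step differs by arm, the recorded risk difference no longer estimates the effect of capnography. At a planned control rate of 8%, a shift of one or two patients per hundred is large compared with the planned 4-point difference.

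**Working it through.** **Inputs.** From Sample size {14}: 8% v 4%, two-sided alpha 5%, power 90%, 1:1 allocation, 10% dropout, about 1800 patients. That is 900 per arm, or 900 × 0.9 = 810 evaluable per arm. The article gives no rate of missed or misclassified events, so losses of 10%, 20% and 30% in one arm are an assumed range.

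**The plan's own figure.** With p̄ = 0.06, the pooled two-proportion formula is

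n = [1.960·√(2·0.06·0.94) + 1.282·√(0.08·0.92 + 0.04·0.96)]² / 0.04² = 739 per arm.

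The continuity correction, n/4·[1 + √(1 + 4/(n·0.04))]², gives 788 per arm, or 1576 in total. Then 1576/0.9 = 1751, or 1752 after rounding up by arm. This is within 3% of the stated 1800, so the inputs are read as intended.

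**Effect of one-sided loss.** For recorded rates p1 and p2 with d = |p1 − p2|, the chance of a significant result is Φ[(d − 1.960·s0)/s1] plus the opposite tail. Here s0 = √(2p̄(1 − p̄)/810) and s1 = √(p1(1 − p1)/810 + p2(1 − p2)/810).

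*True rate 8% in both arms; events lost in the capnography arm only:*

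| Lost | Patients (of about 65) | Recorded rates | Chance of p < 0.05 |
|---|---|---|---|
| 0% | 0 | 8.0% v 8.0% | 5.0% |
| 10% | 6.5 | 8.0% v 7.2% | 9.3% |
| 20% | 13.0 | 8.0% v 6.4% | 23.8% |
| 30% | 19.4 | 8.0% v 5.6% | 48.4% |

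For the 20% row: d = 0.016, s0 = s1 = 0.01284, (0.016 − 0.02517)/0.01284 = −0.715, Φ = 0.237; the other tail adds 0.001.

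*True rates 8% v 4%; events lost in the control arm only:*

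| Lost | Recorded rates | Power |
|---|---|---|
| 0% | 8.0% v 4.0% | 92.4% |
| 10% | 7.2% v 4.0% | 80% |
| 20% | 6.4% v 4.0% | 59% |
| 30% | 5.6% v 4.0% | 33% |

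**What it takes to decide the result outright.** These are chi-square tests on expected counts at 810 per arm; ranges cover the test without and with continuity correction.

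- To create a difference from 65 v 65, recorded events in one arm must fall to 45 or 44. That is 20–21 of 65, or 31–32%.
- To hide 65 v 32, control must fall to 50 or 49. That is 15–16 of 65, or 23–25%.
- At 900 per arm the figures are 21–22 of 72 (29–31%) and 17–18 of 72 (24–25%).

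So roughly 25–30% of one arm's events must be recorded differently before the conclusion flips on expected counts. Smaller losses distort the error rates without settling the result.

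**The case against.** The strongest reply has several parts.

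- SpO2 is a numeric reading taken in both arms, the category limits are numeric, data collectors are trained, sites are visited for quality control, and data are monitored before lock. This stands as mitigation, but none of it masks anyone.
- The treating team cannot be masked to a monitoring intervention. This also stands. The avoidable part is the classification, not the care.
- A reader might infer that the Table 2 tick-box is the source of the primary outcome. The documents do not say so. Outcomes {12} assigns that tool to other adverse events, and Table 3 lists hypoxia and adverse events on separate rows. The case report form is not shown and may already hold numeric values.
- A reader might infer that small differential recording is enough to create or hide the effect, or that the bias must favour capnography. Neither is supported. The 10–30% range is assumed, a 10% loss moves the false-positive rate only from 5% to about 9%, and closer watching in the capnography arm could equally raise recording there.
- Most of the modelled harm is events never recorded, which hand-filled fields cannot recover. This is correct and limits what the fix can do.

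A reader might also take the text under Table 3 in Participant timeline {13} as proof that the endpoint is measured differently by arm. For the capnography group it says "the definition of hypoxia is 75%<SpO_2_ < 90%, <60s"; then "In the control group, hypoxia is defined as SpO_2_ <90"%, with no lower bound or duration. The surrounding text concerns what prompts an intervention, so it does not establish how the outcome is recorded. It is a separate inconsistency with the outcome section, and the passages must be reconciled.

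**Conclusion.** The point holds as a risk that can be reduced cheaply, not as a demonstrated bias. The article fixes that only participants are blinded, makes the primary outcome depend on a saturation band and a 60 s limit, concedes possible bias, and describes no masked classification. That staff who know the arm do the classifying follows from the blinding statement; the article does not name who they are.

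The size rests on three assumptions: 810 evaluable per arm, the planned rates, and loss confined to one arm. On those, losses of 10–30% would raise the false-positive rate to about 9–48% or cut power to about 80–33%. The true amount and direction of any differential recording are unknown.

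**What to change.** 1. In both arms, record for each episode the lowest SpO2 and the seconds below 90%, exported from the monitor where it can do so.
2. Derive hypoxia, subclinical and severe categories with one fixed program that applies the definitions in Outcomes {12} identically to both arms.
3. Have the existing data manager run it on data without the arm code, and lock the classification before unmasking.

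**Cost.** Two numeric fields, one program and slightly more recording per episode. Sample size, procedures and staffing do not change.

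**Timing.** Trial status gives a start in September 2021 and recruitment to December 2023. If recruitment is under way, this needs an amendment with ethics committee consent, and capture would differ before and after it. In that case apply the program to the numeric values available and report which patients had them.

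**Limit.** Hand-read values remove discretion over the category but not over noticing or timing a dip. Only monitor export would address that, and the article does not say whether the monitor's data are stored or exportable.
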